### Sample size estimates

PASS (Version 15.0) software was utilized for sample size determination. The primary study outcomes encompass the incidence of in-hospital DCI and CVS, both exhibiting nearly equivalent prevalence rates. Drawing from our current retrospective and prospective data, we anticipate a prevalence of 23% in the experimental group and 45% in the control group. With a significance level (*α*) of 0.05 and a desired statistical power of 90%, the necessary sample size per study arm to discern this difference is calculated to be 103 patients.

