### Statistical analysis

We will conduct data analysis in accordance with the intention-to-treat principle. Continuous variables will be presented as mean ± standard deviation (SD) or median along with interquartile range (IQR). Categorical variables were summarized as frequency (percentage). Continuous variables will be assessed using either the independent Student’s *t*-test (assuming normal distribution) or the Mann–Whitney *U* test. Dichotomized variables will be compared utilizing the Pearson chi-square test or Fisher’s exact test. To mitigate preoperative confounding factors, a multiple regression analysis will be employed to compare outcomes between the two groups. The results will be reported as adjusted odds ratios (OR) accompanied by 95% confidence intervals (CI), with OR values below 1 indicating a treatment effect in favor of hydrogen–oxygen mixture therapy. Postoperative follow-up assessments at designated time intervals are imperative, and the absence of data should not be anticipated. Statistical significance will be defined as a threshold of *P* < 0.05.

Subgroups analysis will be performed, including subgroup by age, sex, WFNS, mFS, and treatment modality. Subgroup analyses are limited to the primary efficacy endpoint and safety endpoint only. Separate logistic models will be applied to each subgroup during subgroup analysis.

There will be no interim analyses in this trial.

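### Subgroup effects are planned as separate logistic models with no stated interaction test, so the stated method does not test whether the treatment effect differs between subgroup levels

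*Protocol article*

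**What the plan says.** The Statistical analysis section of the protocol article names the factors: "Subgroups analysis will be performed, including subgroup by age, sex, WFNS, mFS, and treatment modality". It limits the outcomes: "Subgroup analyses are limited to the primary efficacy endpoint and safety endpoint only". It then gives the method: "Separate logistic models will be applied to each subgroup during subgroup analysis". The only decision rule in the section is general: "Statistical significance will be defined as a threshold of" P < 0.05.

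The article states no interaction or heterogeneity test, no multiplicity adjustment for subgroups and no exploratory label for them. Cut-points and the number of levels per factor are not given. Two primary outcomes are defined (in-hospital DCI and in-hospital CVS), so each factor is examined on at least two efficacy outcomes as well as safety.

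**The concern.** A subgroup analysis is meant to show whether the treatment effect varies with a patient characteristic. That is a comparison between levels. Separate models give an estimate and a P value within each level, and no test of the comparison. With a general 0.05 threshold as the only stated criterion, a reader is left to set one within-level P value against another.

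That is a poor guide in a trial of this size. The sample is planned for about 90% power in all patients, so each level of a factor has far less. One level will then often reach significance while the other does not, even when the effect is identical in both. The article itself says that positive findings from this single-centre study will need external validation. A spurious statement that hydrogen works only in one grade or one treatment modality could misdirect that validation. The primary comparison is not affected.

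**Working it through.** **Inputs from the documents.** Event rates: "we anticipate a prevalence of 23% in the experimental group and 45% in the control group" (Sample size estimates). 103 per arm, 206 in total (Patient population; Sample size estimates). Threshold 0.05 and five factors (Statistical analysis).

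**Assumptions.** Two-sided tests; two levels per factor; splits of 50:50 and 70:30 as a range; factors independent of each other and of outcome; unadjusted tests; the same true effect in every level.

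**Step 1: the plan's own figure.** For 45% vs 23%, two-sided 0.05 and 90% power, the usual two-proportion formula gives 96 per arm, or 105 with continuity correction. The stated 103 is within two patients of the latter.

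**Step 2: power within a level.** With n per arm, p̄ = 0.34 and d = 0.22:

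power = Φ{[d − 1.96·√(2p̄(1−p̄)/n)] / √[(0.23·0.77 + 0.45·0.55)/n]}

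- All patients, n = 103: (0.22 − 0.1294)/0.0642 = 1.41, power 92%.
- Half of the patients, n = 51.5: (0.22 − 0.1830)/0.0908 = 0.41, power 66%.
- 70:30 split, n = 72.1 and 30.9: power 80% and 45%.

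**Step 3: chance that exactly one of two levels is significant.** This is a(1−b) + b(1−a), where a and b are the two powers.

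- 50:50: 2 × 0.658 × 0.342 = 45%.
- 70:30: 0.803 × 0.555 + 0.445 × 0.197 = 53%.

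**Step 4: five factors.** All factors are cut from the same patients, so the results are correlated. Treating them as independent would give 1 − 0.55⁵ = 95% at 50:50, which is too high. Simulation (6,000 to 20,000 trials per scenario) keeps the correlation. The comparator is a Wald test of the difference in log odds ratios at 0.05.

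| True effect, the same in all levels | Separate models: one level significant, the other not, per factor | Separate models: any of five factors, one outcome | Interaction test: any of five, one outcome |
|---|---|---|---|
| 45% vs 23% (50:50 to 70:30) | 44–53% | 78–90% | about 20–21% |
| 45% vs 34%, half the effect (50:50) | 33% | 64% | about 22% |
| No effect | about 10% | about 29% | about 21–22% |

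Per factor, the interaction test gives a false difference in about 4–5% of trials in every row. Counting both DCI and CVS, at least one split from separate models occurs in 93–99% of trials at the planned effect and in about 49% with no effect.

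**Step 5: what the interaction test can detect.** At the planned rates and a 50:50 split, the variance of the log odds ratio in one level is (1/0.1771 + 1/0.2475)/51.5 = 0.188. The difference between levels has variance 0.376 and standard error 0.613. For 80% power the log odds ratios must differ by (1.96 + 0.84) × 0.613 = 1.72, a ratio of odds ratios of about 5.6. The planned overall odds ratio is (0.23 × 0.55)/(0.77 × 0.45) = 0.37, so only a very large difference between levels would be found reliably.

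**The case against.** **Silence is not exclusion.** This is a condensed article, and an analysis plan that is not shown may add an interaction test. A reader might infer that the sponsor has ruled one out; the article does not say so. What stands against this is that the article does not defer the subgroup method. It states one, and the one it states does not compare levels. Nothing in the text points to a further test.

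**The wording has a second reading.** The list of factors runs "including subgroup by age, sex, WFNS, mFS, and treatment modality", so the word subgroup may denote the factor, and the sentence could mean one model per factor. One model per level is the more natural reading. On the other, the sentence still names no interaction term, and a model without one gives a single treatment effect and no subgroup result.

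**Chance differences as the usual outcome.** A reader might infer that the analysis will usually produce chance differences whatever the truth. The figures do not support that. It holds for the set of five factors when the treatment works at the planned effect or half of it. With no effect, the figure is about 29% on one outcome. For a single factor, it is close to half even at the planned effect. Nor does the article say that claims will rest on within-level P values, so how the results would be written up cannot be predicted from it.

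**Multiplicity is a separate matter.** With no effect, at least one significant level appears in about 29–30% of trials on one outcome. Some interaction is significant in about 21–22%. The change therefore does little in that case; its large benefit comes when the treatment works.

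**Odds ratios and confidence intervals soften the problem.** The article will report adjusted odds ratios with 95% CIs. At the planned effect and a 50:50 split, both levels of a factor favour hydrogen in about 98% of simulated trials, and the two intervals overlap in over 99%. A careful reader is less exposed than the counts of significant and non-significant results suggest. This is a good reason to keep level-specific estimates, and none to omit the test of their difference.

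**Conclusion.** The point holds in a limited form. The stated method does not test whether the treatment effect differs between subgroup levels. If the effect is uniform and as planned, contrasting within-level significance would suggest a difference in roughly half of trials per factor and in most trials over five factors. An interaction test brings this to about one in twenty per factor and one in five over the five factors. That remainder is multiplicity, so the exploratory label is needed as well.

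The figures rest on two-level, independent factors split between 50:50 and 70:30, which the article does not specify. A more uneven split raises the per-factor figure at the planned effect (80:20 gives 63%), and extra levels of WFNS or mFS, or safety outcomes, would add comparisons. The matter should be corrected, but it does not touch the primary analysis or the sample size.

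**What to change.** Replace the sentence on separate models with wording such as: For each subgroup factor, one logistic model will be fitted in all randomized patients with treatment, factor and treatment-by-factor interaction, and the same covariates as the main adjusted model (including WFNS where it is not itself the factor). Odds ratios with 95% CIs for each level will be derived from this model and reported with the interaction P value. All subgroup results are exploratory, and no subgroup claim will be based on a P value within a level.

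The cost is a short change of text; the data, software and number of patients stay the same. The downside is low power at 206 patients, so the report should also say that a non-significant interaction does not show that the effect is the same in all levels.

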### Patient and public involvement

Patients or the public have not participated in the design or execution of our research. Upon study completion, a manuscript will be prepared to present the trial findings. The final study results will be disseminated to all participants through the methods communicated at enrollment (mobile phone, WeChat, email, etc.).

### Study timeline

We anticipate that the study will span a duration of 24 months. Commencing in mid-June 2022, patient enrollment is expected to span a period of 18 months. An additional 6 months will be allocated for the meticulous tasks of data cleaning, in-depth analysis, and the preparation of the manuscript.

## Discussion

HOMA represents a single-center, prospective, open-label, and randomized controlled clinical trial, aimed at assessing the potential of hydrogen–oxygen gas mixture inhalation therapy in averting DCI or CVS while ameliorating outcomes in patients afflicted by aSAH. It is worth noting that this constitutes the first large-scale clinical trial of hydrogen therapy as applied to aSAH patients.

The Chinese population accounts for approximately one-fifth of the global population. With the advent of the aging demographic epoch, the incidence of stroke has been on a steady rise, posing a significant menace to public health. Consequently, the optimization of patient care has assumed paramount importance within the healthcare system.

Given the current impasse in substantially improving outcomes for aSAH patients, clinicians should be prompted to initiate additional prospective clinical trials. Recent years have witnessed the unequivocal validation of hydrogen has therapeutic potential in basic research [26, 27]. We posit that hydrogen’s therapeutic attributes closely align with the concept of EBI following aSAH. Therefore, we embarked on the utilization of hydrogen therapy in aSAH patients, with the aim of elucidating potential mechanisms underlying post-aneurysm rupture bodily damage.

## Trial status

This research protocol version 1.0 (2022/05/07) is approved, and recruitment of patients for this HOMA trial has begun in September of 2022 and is expected to complete in March of 2024.

## Abbreviations

aSAH: Aneurysmal subarachnoid hemorrhage
DCI: Delayed cerebral ischemia
CVS: Cerebral vasospasm
EBI: Early brain injury
OR: Odds ratios
CI: Confidence intervals
DSMB: Data Safety Monitoring Board
GCS: Glasgow Coma Scale
WFNS: World Federation of Neurological Societies
VEGF: Vascular endothelial growth factor
ET-1: Endothelin-1
TCD: Transcranial Doppler
SEBES: Subarachnoid Hemorrhage Early Brain Edema
mFS: Modified Fisher scale
CRP: C-reactive protein
